## 2.8 Study Procedures

Eligible participants will sign the consent form at the physician’s office, and laboratory results will be recorded as baseline data. If the patient’s medical record does not contain recently updated laboratory tests from the previous three months, laboratory tests will be scheduled for blood sample collection in the clinic and tested in Abu Dhabi Health Services Company (SEHA) central laboratory, and the same process will be performed at the conclusion of the follow-up period after 12 months. Laboratory tests in the study protocol included gylcated hemoglobin A1c (HbA1c), estimated Glomerular Filtration Rate (eGFR), complete blood count, electrolyte panel including potassium and magnesium levels, serum creatinine levels, and albumin/creatinine ratio.

Laboratory and clinical assessments in the study protocol included BP measurement and laboratory tests HbA1c level, low-density lipoprotein cholesterol (LDL-C) level, complete blood count, electrolyte panel including K and Mg levels, eGFR, serum creatinine level, and albumin/creatinine ratio. BP measurements and laboratory tests will be performed according to the standard procedures for BP measurement and blood sample withdrawal at the clinic.

In addition, each participant in both groups will undergo individual assessments at initial visit and study exit including medication adherence by clinical pharmacist and diet and exercise assessment by specialized dietician.

During the study period, the control group will receive the usual care provided in the clinic including the routine follow-up and clinical assessments (as needed). The routine usual care will include follow-up schedule every 3 months with the treating physician, vital signs monitoring in the visited clinic, physician consultation, any additional investigational services or laboratory tests requested by the treating physician depending on each patient’s condition, patient counselling at the pharmacy counter, dietitian counselling service if requested by the patient or referred by the treating physician, and a call reminder from the clinic call centre 3 days before the appointment.

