Each participant in the intervention group will receive a 15- to 30-min counselling session at the initial visit and each scheduled follow-up visit which will occur every 3 months. During these sessions, the pharmacist will assess medication adherence with a validated adherence questionnaire (Appendix 3) and counsel the patients on the importance of medication adherence on clinical outcomes. The barriers to medication adherence will be identified, discussed with the patient, and resolved as much as possible. Finally, the patient will be provided with two or three months of medication supply, and the medication refill date will be documented for medication adherence calculation using the medication possession ratio (MPR) [42, 43].

After each visit, each participant in the intervention group will receive a 15-minute follow-up phone interview within two weeks for adherence reinforcement and to address any non-compliance issues or medication side effects. Moreover, they will be scheduled for their next medication refill and follow-up visits in the clinic appointment system. Appointments will be scheduled at months 3, 6, and 12 from the initial visit according to the patient’s preferred date, and they will receive a reminder phone call three days before the next visit from the clinic call centre.

Medication adherence will be evaluated using two techniques during the follow-up period: calculating the medication adherence possession ratio and the medication adherence questionnaire scores.

1. Medication Adherence Possession Formulas

In this study, we will use three formulas to calculate medication adherence from patients’ medication refills recorded in Salamtak:

1. Total Fixed Medication Possession Ratio (MPRt)

A fixed medication possession ratio (MPR) formula will be used to measure total (composite) adherence to all medications (MPRt) [44, 45]. The MPRt will be calculated for three chronic regimens including antihyperglycaemic, antihypertensive and antihyperlipidaemic regimens.

For the total MPRt, no regimen-specific MPR (MPRs) will be measured. It is calculated by summing the days’ supply of medication per prescription, then dividing by the number of days of patient follow-up, using a fixed follow-up period of 365 days (12 months) as a constant denominator, adjusted to hospital stay if the participant was admitted during the follow-up period (Figure 2).

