$$\text{MPR}\text{t}\text{ }\text{=}\frac{\sum_{i = 0}^{End of follow-up period} \text{Days of supply Rxi}}{\text{Days of follow-up period}}$$

$\text{MPR}\text{t}\text{ }\text{=}$

Figure 2: Fixed total medication possession ratio (MPRt) calculation

For the above example, if the patient had a medication supply equal to 345 days (90 days + 75 days) during the fixed follow-up period of 365 days, the MPRt calculated as 345/365 = 0.95.

1. Regimen-specific Medication Possession Ratio (MPRs)

Regimen-specific MPR (MPRs) will be calculated for all three regimens (antihyperglycaemic, antihypertensive, and antihyperlipidaemic), whether any or all were contained in the patient’s medication profile [46, 47].

The denominator for MPRs also covers the follow-up period of 12 months but will be calculated based on the last refill date for a specific medication regimen (for any medication class) minus the first refill date for any medication in the regimen, even if this medication was in a different class from the medication used in the last refill. In addition, medications within the same regimen will be considered interchangeable (even if they belonged to different medication classes).

$$\text{MPRs}\text{ }\text{=}\frac{\sum\text{Days of supply of }\text{medication}\text{ in a regimen}}{\text{Last refill date‐First refill date} \left( \text{for specific regimen} \right)}$$

Of note, for both types of MPR (MPRt and regimen-specific MPRs), if the patient had refilled medication prior to the date of joining the study, MPR will be calculated from the date of signing the consent, excluding the supply from the last prescription or medication refill and will be capped at 1, and medication adherence (either MPRt or MPRs ) will be calculated after 12 months of follow-up [42].

The standard adherence threshold of 0.80 MPR will be used as a lower bound for mediation adherence [45], with MPR = 1 indicating perfect adherence, MPR < 0.80 indicating patient non-adherence, and MPR= 0 indicating no adherence. The patients’ medication refills for each medication class will be recorded from Salamtak (including records from private and governmental pharmacies) at each follow-up visit.

1. Regimen Non-persistence Possession Ratio (RNP)

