## 2.10 Statistical Analysis

The sample size required to reach significant in the three primary outcomes in the study’s multi-intervention approach is 180 participant (90 participants in each group). Sample size was calculated with Giga sample size online calculator [69], according to a pilot analysis of 50 participants matching study protocol, with a power of 80% with alpha level of 5% to detect the minimal difference of each primary outcomes in the study.

For 1^st^ outcome, the baseline medication possession ratio (MPR) for those 50 participants was 0.93 ± 0.09 (mean ± SD), we determined that a target of 82 participants per group would be required for a minimum detectable effect of 0.035 between both groups. A total sample size of 180 was calculated, assuming dropout rate of 10% in both groups.

For 2^nd^ outcome, the mean body mass index (BMI) (mean ± SD) of the 50 participants was 31.2 ± 6.4, and the total number of participants required to detect minimum detectable difference of 2.5 in BMI between groups was 180 participants, powered for 80% with α equal to 0.05, considering drop rate of 10% throughout the study period.

In addition, for 3^rd^ outcome to detect minimal difference of 0.5% in HbA1c between groups with mean HbA1c = 7.7 ± 1.3 (mean ± SD) at baseline (for the same 50 participants), a total sample size of 184 participants were calculated with 84 participants per group were required, considering 10% expected dropout rate during the follow-up period.

For data analysis, the difference between both groups will be tested for normality using the Shapiro–Wilk test. Data will be presented as percentages for categorical variables or mean ± SD or median (25th, 75th percentiles) for continuous variables. Chi-square test will be used for the categorical variables, whereas student’s t-test will be used for normally distributed continuous variables, or Mann–Whitney U test for non-normally distributed continuous variables.

Analyses will be performed using IBM SPSS Statistics (version 26), and differences will be considered significant for a p-value of <0.05.

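### MPRt counts every fill's full supply over a fixed 365 days but drops stock held at consent, so numerator and denominator cover different windows

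*Protocol*

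**What the plan says.** Section 2.8.1 gives the rule for MPRt in words and as a formula. The words sum the days' "supply of medication per prescription, then dividing by the number of days of patient follow-up, using a fixed follow-up period of 365 days", with an adjustment for hospital stay. The formula sums the days of supply of each prescription up to the end of follow-up.

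For patients who refilled before joining, the ratio runs from the consent date, "excluding the supply from the last prescription or medication refill and will be capped at 1". In context the excluded supply is the last refill before the study.

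The worked example reads "if the patient had a medication supply equal to 345 days (90 days + 75 days) during the fixed follow-up period of 365 days" and arrives at 0.95. An MPR below 0.80 is classed as non-adherent.

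On dispensing, the counselling text for the intervention group says "the patient will be provided with two or three months of medication supply" at its sessions, which include the initial visit, and "Appointments will be scheduled at months 3, 6, and 12 from the initial visit". Figure 1 shows visits at months 1, 3, 6, 9 and 12 and labels month 12 as close-out. For controls, section 2.8 says "The routine usual care will include follow-up schedule every 3 months with the treating physician". Their days' supply, and any dispensing at entry or exit, are not stated.

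Section 2.10 sizes the first primary outcome on MPR: "a target of 82 participants per group would be required for a minimum detectable effect of 0.035 between both groups". The protocol does not name MPRt as the primary adherence variable in so many words. It is the natural reading, because section 1.3 lists regimen-specific MPR as secondary.

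**The concern.** The denominator is the 365 days after consent. The numerator leaves out stock that covers the first of those days and includes stock that covers days after the last of them. The two errors have opposite signs, and nothing makes them equal within a patient or between arms.

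The cap at 1 limits the result but does not repair it. Surplus supply from the end of the year first fills real gaps from earlier in the year and only then reaches the cap.

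Three things are at stake: a planned difference of only 0.035 (0.035 × 365 = 12.8 days), classification at the 0.80 threshold, and a ceiling that can flatten a real difference.

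**Working it through.** **Inputs from the protocol.** Denominator 365 days, cap 1 and threshold 0.80 (section 2.8.1). Supply of two or three months per session, taken as 60 or 90 days (section 2.8.1). Baseline MPR 0.93, SD 0.09, difference 0.035, power 80%, alpha 5%, 82 per group (section 2.10).

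**The plan's own figures.** n per group = 2 × (z_alpha + z_beta)² × SD² / difference². One-sided: 2 × (1.645 + 0.842)² × 0.09² / 0.035² = 81.8, so 82 as stated. (Two-sided it is 104. Sidedness is not the point here; the match confirms that 0.035 and 0.09 are the planning inputs.) Worked example: 345/365 = 0.945, but 90 + 75 = 165 and 165/365 = 0.452. The listed parts therefore give a non-adherent patient, the stated total an adherent one. The sum 3 × 90 + 75 = 345 would work.

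**Single patients** (one drug, 90-day fills, consent on day 0):

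- Fills on days 0, 100, 200, 300. Rule: 360/365 = 0.986. Covered: (90 + 90 + 90 + 65)/365 = 335/365 = 0.918. Excess 0.068.
- Fills on days 0, 120, 240, 350. Rule: 360/365 = 0.986. Covered: (90 + 90 + 90 + 15)/365 = 285/365 = 0.781. The patient moves from non-adherent to adherent.

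**Averages.** Refill simulation with assumed exponential gaps between fills, set so that long-run coverage is 0.93. Stock at consent, where present, is uniform between 0 and one full fill.

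| Fill | Stock at consent | Exit fill counted | Share of year covered | Rule as written | Day-365 cut only |
|---|---|---|---|---|---|
| 60 d | no | no | 0.938 | 0.986 | 0.938 |
| 90 d | no | no | 0.944 | 0.986 | 0.944 |
| 60 d | yes | no | 0.930 | 0.926 | 0.848 |
| 90 d | yes | no | 0.930 | 0.926 | 0.808 |
| 60 d | no | yes | 0.938 | 1.000 | 0.938 |
| 90 d | no | yes | 0.944 | 1.000 | 0.944 |
| 60 d | yes | yes | 0.931 | 0.995 | 0.849 |
| 90 d | yes | yes | 0.930 | 0.997 | 0.807 |

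- Day-0 start, no exit fill: overstated by 0.048 (60 d) and 0.042 (90 d).
- Stock at consent, no exit fill: 0.926 − 0.930 = −0.004. Dropped carry-in and counted overhang cancel.
- Exit fill counted: about 1.0 in every case.
- Day-365 cut alone, stock at consent: understated by 0.082 (60 d) and 0.122 (90 d).

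**Exit fill without a refill model.** Uncapped, it adds 60/365 = 0.164 to 90/365 = 0.247. With the cap, a patient at 0.93 can gain at most 0.07. Averaged over a beta distribution with mean 0.93 and SD 0.09 (assumed shape), the gain is 0.057 (60 d) to 0.065 (90 d), with 87% to 94% of patients at 1.0.

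**What this could do between arms.** Suppose, as an assumption, that one arm is first filled on day 0 and the other holds stock, with the same refill behaviour and no exit fill. With 90-day fills the rule shows 0.986 − 0.926 = 0.060, against a true difference of 0.944 − 0.930 = 0.014. Cutting only at day 365 would widen the apparent difference to 0.944 − 0.808 = 0.136. If both arms have a counted exit fill, both sit near 1.0 and a real difference disappears.

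**The case against.** A reader might infer that MPRt overstates adherence by more than the planned effect, mainly in the intervention arm, because that arm is dispensed to at month 12 and controls are not. The documents do not support this.

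- **Arms.** Controls have three-monthly physician follow-up and an exit assessment. The sentence "The patients’ medication refills for each medication class will be recorded from Salamtak" is not limited to one arm. Control dispensing is unspecified, which is not the same as absent.
- **Month 12.** Dispensing there is inferred from the general sentence about counselling sessions. Figure 1 calls the visit close-out, and the timeline in section 3 puts the intervention phases at months 3, 6 and 9.
- **Day-0 fill.** Section 2.6 identifies intervention patients a week before their next refill or visit, and section 3 starts the first intervention phase three months after entry. Section 2.4 requires 12 weeks of unchanged therapy, so many patients probably hold stock at consent. For them the rule as written is close to right.

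These three points stand, and they limit the conclusion.

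Two others carry less weight. The worked example speaks of supply during follow-up, and its 75-day part may be a last fill cut at day 365. That is a hint in an example that does not add up (its drawing is not available here), and neither the rule nor the formula contains a cut. It may also be said that truncation belongs in an analysis plan and that untruncated MPR is an accepted variant. But the protocol fixes this derivation itself, and an untruncated numerator beside a start-of-window exclusion remains a mismatch.

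**Conclusion.** The concern holds as a mismatch of windows, not as a demonstrated bias towards one arm. Applied literally, the rule can score 0.986 for a patient covered for 0.781 of the year.

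On average, the shift runs from about zero (stock at consent, no exit fill) through 0.04 to 0.05 (first fill on day 0) to about 0.06 to 0.07 (exit fill counted). All but the first exceed the planned 0.035. The direction of any effect on the arm comparison depends on dispensing at entry and exit, which the protocol does not specify for controls.

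The single-patient results are plain arithmetic. The averages rest on assumed exponential gaps, 0.93 coverage, 60- or 90-day fills and an assumed distribution of stock. The text should be changed before MPRt is derived.

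**What to change.** In section 2.8.1 and Figure 2, define the MPRt numerator, identically in both arms, as the days of supply that fall within days 1 to 365 after consent:

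1. Count the unexpired days of the last pre-consent fill from consent onward. This replaces the clause that excludes it and removes the doubt about which prescription is the last one.
2. Cut each fill at day 365. With consent as day 1, a fill contributes the smaller of its days' supply and 366 minus the fill day.
3. Do not count supply dispensed at the exit visit.
4. Keep the cap at 1 and the hospital-stay adjustment.

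Steps 1 and 2 belong together. Step 2 alone would understate patients with stock at consent by about 0.08 to 0.12 and could widen a spurious arm difference. Step 3 and the corrected example are sound on their own.

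Correct the example so that its parts give the total: three 90-day fills plus 75 in-window days of a fourth (filled on day 366 − 75 = 291) make 345/365 = 0.95 and also show the cut. The visit months in section 2.8.1 and in Figure 1 must be reconciled, and the protocol should state what is dispensed at entry and exit in each arm.

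The cost is a few sentences and the date and supply of the last pre-consent fill, which should be in Salamtak with the other refills. The downside is less comparability with studies that report untruncated MPR. The pilot mean and SD may also not carry over exactly, since the protocol does not say how the pilot MPR was derived.

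### As printed, the two medication possession ratios can score partly supplied patients as perfectly adherent, and the pilot planning figure appears to come from a different calculation

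*Protocol*

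**What the plan says.** All formulas are in Protocol section 2.8.1.

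- **MPRt, scope.** "The MPRt will be calculated for three chronic regimens including antihyperglycaemic, antihypertensive and antihyperlipidaemic regimens". It is a composite over all medications, and no averaging of regimen ratios takes place inside it: "For the total MPRt, no regimen-specific MPR (MPRs) will be measured".
- **MPRt, formula.** It sums the days' "supply of medication per prescription, then dividing by the number of days of patient follow-up, using a fixed follow-up period of 365 days". The 365 days serve "as a constant denominator, adjusted to hospital stay if the participant was admitted during the follow-up period". The displayed equation is one sum over prescriptions divided by follow-up days.
- **MPRt, example.** "if the patient had a medication supply equal to 345 days (90 days + 75 days) during the fixed follow-up period of 365 days", giving 0.95.
- **MPRs.** The denominator is the "last refill date for a specific medication regimen (for any medication class) minus the first refill date for any medication in the regimen". The numerator adds all supply in the regimen, and "medications within the same regimen will be considered interchangeable (even if they belonged to different medication classes".
- **Both ratios.** They are limited to 1. A value of 1 is labelled perfect and a value under 0.80 non-adherent. A clause about refills made before joining the study also leaves out the supply of a last fill, without making clear which one.

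Section 1.3 makes medication adherence the first primary outcome and regimen-specific MPR a secondary one. Section 1.4 names the fixed MPR equation and a questionnaire as the adherence measures. Section 2.10 sizes the first outcome on a pilot MPR of 0.93 ± 0.09, a detectable difference of 0.035 and 82 patients per group, without saying which MPR is meant.

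**The concern.** A possession ratio should fall when supply is missing. In the printed MPRt the numerator can grow with the number of concurrent regimens, while the denominator stays at one calendar year and the limit of 1 hides the excess. In MPRs the denominator ends at the last refill, so the time after a patient stops collecting medication drops out. Within a regimen, drugs taken together add their days as if they followed one another.

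If the formulas are applied as written, patients on several drugs pile up at 1, and a real difference between arms shrinks toward zero. If they are not applied as written, the document does not define the quantity on which the first primary outcome was sized.

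**Working it through.** **The plan's own figures.** 345/365 = 0.945, printed as 0.95, so the ratio reproduces. The bracket does not: 90 + 75 = 165, and 165/365 = 0.45. A single stream of 90 + 90 + 90 + 75 = 345 would explain the total, but that is inference, and the accompanying figure is not shown. The 82 per group follows from SD 0.09 and difference 0.035 at one-sided 5% and 80% power: 2 × (1.645 + 0.842)² × (0.09/0.035)² ≈ 81.8. At two-sided 5% it would be 104. Either way, the planning rests on the pilot SD.

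**MPRt as printed.** With k regimens and average coverage c, the score is min(1, k × c). It reaches 1 at c = 1/k and 0.80 at c = 0.80/k:

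| Regimens | Coverage that scores 1 | Coverage that scores 0.80 |
| --- | --- | --- |
| 1 | 1.00 | 0.80 |
| 2 | 0.50 | 0.40 |
| 3 | 0.33 | 0.27 |

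Constructed patients on three regimens:

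| Days supplied | Sum/365 | Score | Mean of the regimen ratios |
| --- | --- | --- | --- |
| 122, 122, 122 | 366/365 = 1.003 | 1.00 | 0.33 |
| 180, 180, 90 | 450/365 = 1.23 | 1.00 | 0.41 |
| 365, 0, 0 | 365/365 = 1.00 | 1.00 | 0.33 |

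**Effect on a difference between arms.** The protocol gives no coverage per regimen, so the inputs here are assumptions: independent normal coverage per regimen, restricted to 0–1.

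| Assumed coverage (SD) | True difference | Score, two regimens | Score, three regimens |
| --- | --- | --- | --- |
| 0.93 vs 0.965 (0.09) | 0.025 | 1.000 vs 1.000 | 1.000 vs 1.000 |
| 0.60 vs 0.75 (0.15) | 0.147 | 0.980 vs 0.999 | 1.000 vs 1.000 |
| 0.50 vs 0.70 (0.15) | 0.199 | 0.915 vs 0.998 | 0.997 vs 1.000 |

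Patients on one regimen are unaffected.

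**Against the pilot.** Under the printed sum, a score of 0.93 corresponds to average coverage of 0.93/2 = 0.465 with two regimens or 0.93/3 = 0.31 with three. A pilot mean of 0.93 with SD 0.09 is easier to obtain from one refill stream, or from an average, than from a sum over regimens.

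**MPRs as printed.** The score is total supply divided by (last minus first refill date), limited to 1.

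- 90-day fills on days 0 and 90, then none: 180/90 = 2, scored 1.00. With the last fill left out: 90/90 = 1.00. Share of the year supplied: 180/365 = 0.49.
- 90-day fills on days 0 and 180: 180/180 = 1.00, or 90/180 = 0.50 with the last fill left out. Here the unclear exclusion clause decides the result.
- One fill only: the denominator is 0 and the ratio is undefined.
- Two drugs of one regimen, both filled for 90 days on days 0 and 180: 360/180 = 2, or 270/180 = 1.5 with one last fill left out, scored 1.00 either way. Each drug covers 180/365 = 0.49 of the year.

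**The case against.** The strongest reply is that the protocol never says in so many words that supplies of concurrent regimens are added. The worked example looks like one refill stream, each visit is described as giving two or three months of supply with one refill date, and the pilot mean points the same way. Section 2.4 requires only diabetes medication, so some patients may have a single regimen. This stands as far as it goes: a reader might infer that the primary outcome is already saturated, and the documents do not show that. They do show a composite over all medications, one sum, a constant 365 and no regimen ratios, so adding is the plain reading of the printed rule.

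Other stronger readings also fail:

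- **The first primary outcome can no longer show non-adherence.** The questionnaire is untouched. That MPRt is the MPR behind this outcome is inferred from sections 1.3, 1.4 and 2.8.1.
- **Early stopping goes unseen everywhere.** That holds for MPRs only. In a single stream, the fixed 365 days of MPRt do penalise it. The text on regimen non-persistence also aims to capture days without medication, although its printed formula shows days of supply.
- **The MPRs definition contradicts its own mention of 12 months.** The sentence can mean refill dates falling within the 12-month window.
- **Collecting one regimen at a visit counts as full supply.** No rule says so.

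Overlap rules are often left to the SAP, which is not shown. Here, however, the protocol itself fixes the numerator, denominators, limit and threshold, and those stated rules give wrong results.

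**Conclusion.** The point holds in this form. Followed as printed, MPRt scores one-third coverage of three regimens, or one-half coverage of two, as perfect. MPRs scores a patient who stops after two 90-day fills as 1.00 against 0.49 of the year, with or without the last fill, and it is undefined after one fill. The MPRs result needs no interpretation. The MPRt result rests on reading the single sum as covering concurrent regimens, and its size depends on how many regimens patients take, which the protocol does not give. The example and the pilot figure suggest that another calculation was used, so the printed formula and the planning figure appear not to match. A secondary outcome is affected directly, and primary outcome 1 through the MPRt only.

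**What to change.** Replace both definitions before the refill data are analysed.

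- **Per drug:** count each calendar day at most once as covered. The window runs from consent (or the prescribed start, if later) to month 12 (or the prescriber's documented stop, if earlier), less hospital days.
- **Within a regimen:** treat a switch as continuous, but do not add the supply of drugs prescribed together. MPRs is the mean over the drugs concurrently prescribed.
- **Across regimens:** MPRt is the mean of these values over the patient's prescribed regimens.
- **Exclusion clause:** state which fill it drops.
- **Planning:** recompute the pilot mean, SD and power statement on this definition, and correct the bracket in the worked example.

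A flat 365-day denominator for every regimen would be simpler but would create a new bias. For fills on days 0 and 90 with a documented stop on day 180, it gives 180/365 = 0.49, whereas the prescribed window gives 180/180 = 1.00. Section 2.8.1 makes deprescribing assessment part of the intervention, so this error could fall mainly on that arm. Counting a day as covered when any one drug of the regimen is in supply would also fall short, because a missing second drug would stay hidden.

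The cost is re-coding refill data already recorded by medication class in Salamtak, retrieving prescription start and stop dates, and restating the planning figure.

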In addition to the MPR calculation, we will estimate the regimen non-persistence (RNP) or days without medication for each regimen (diabetic, hypertensive, and antihyperlipidaemic regimens) the patient had during the study [48], calculated as the total number of days the patient did not receive one or more medications for any of the patient’s chronic regimen divided by the total follow-up days.

$$\text{RNP}\text{ }\text{=}\frac{\sum\text{Days of supply of medication in a regimen}}{\text{Days of follow-up period}}$$

1. Medication Adherence Questionnaire

A validated medication adherence questionnaire translated into Arabic, showing sufficient reliability with adequate internal consistency, will be used initially to measure medication adherence at baseline for all study participants, and subsequently at each follow-up visit in the intervention group and again at the study exit (Appendix 3)[41].

The questionnaire contains four medication adherence questions from the validated Arabic version of the tool: 1) “Do you ever forget to take your medicine?” and 2) “Are you careless at times about taking your medicine?”, 3) “When you feel better do you sometimes stop taking your medicine??”, 4) “Sometimes if you feel worse when you take the medicine, do you stop taking it?”.

The total score of the medication adherence questionnaire included the first four questions with scores ranging from 0 and 4, with “Yes” having score = 1 and “No” = 0. Increased levels of adherence correspond with lower scores. Patient scores from 3 to 4 will be classified as low adherence, moderate adherence (score from 1 to 2), and high adherence (score = 0, with no answers with yes) [49] (Table 1).

Table 1: Medication adherence questionnaire scoring scheme

| Adherence questionnaire scores |
| --- |
| High adherence = 0 item answered “Yes” |
| Moderate adherence= 1 or 2 items answered “Yes” |
| Low adherence= 3 or 4 items answered “Yes” |

1. Medication Therapy Management (MTM) Program

As a new component of the MPIP, the MTM program will be made available to the clinic’s ambulatory service for the first time, and the intervention group will receive the following interventions as part of the program:

- 1. Medication counselling and reconciliation

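### The displayed formula for regimen non-persistence (RNP) counts days with medication, while the sentence above it defines RNP as days without

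*Protocol*

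**What the plan says.** Section 2.8.1 announces three refill-based formulas: the total possession ratio (MPRt), the regimen-specific possession ratio (MPRs) and the RNP.

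- **RNP in words.** The protocol says "we will estimate the regimen non-persistence (RNP) or days without medication for each regimen", and that this is "calculated as the total number of days the patient did not receive one or more medications". The sentence adds that the count may concern any chronic regimen the patient has, and that it is "divided by the total follow-up days".
- **RNP as displayed.** The formula directly below has the sum of "Days of supply of medication in a regimen" over "Days of follow-up period". It contains no subtraction and no term for gap days.
- **MPRt, for comparison.** "It is calculated by summing the days’ supply of medication per prescription, then dividing by the number of days of patient follow-up". The denominator is held constant at 365 days. The protocol's worked case is 345 days of supply, giving 0.95.
- **Direction of the possession ratio.** It is read "with MPR = 1 indicating perfect adherence, MPR < 0.80 indicating patient non-adherence, and MPR= 0 indicating no adherence".
- **Other rules.** The cap at 1 is stated for MPRt and MPRs only. In the MPRs definition, medications of the same regimen are treated as interchangeable, even across drug classes.

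**The concern.** The name, the gloss and the verbal definition all describe time without drug. The displayed numerator describes time with drug. It is the same numerator as in the MPRs formula, so it looks like a copy in which the inversion was left out.

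At stake is the direction of a derived variable. An analyst who codes the display would obtain a non-persistence value that rises as supply improves. An arm with better refill coverage would then show higher non-persistence, in apparent conflict with the MPR results beside it. RNP would also lose its purpose. It is introduced as an addition to the MPR, but as printed it adds nothing beyond a possession ratio for each regimen over the whole follow-up.

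**Working it through.** **Inputs**, all from section 2.8.1: follow-up 365 days; the worked example of 345 days of supply; the adherence threshold of 0.80, which is 0.80 × 365 = 292 days.

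**The protocol's own figure.** No numerical RNP is given. The MPRt example does reproduce: 345/365 = 0.945, or 0.95 rounded. I take the 345 days as stated. The two fills listed in brackets beside it add to only 165 days, but the figure that may show further fills is not available, and nothing here depends on that breakdown.

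**Formulas**, for one drug with non-overlapping fills and S days of supply:

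- As displayed: RNP = S / 365
- As worded: RNP = (365 − S) / 365

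| Days of supply S | Displayed formula | Verbal definition |
|---|---|---|
| 365 (full supply) | 1.000 | 0.000 |
| 345 (protocol's example) | 0.945 | 20/365 = 0.055 |
| 292 (threshold 0.80) | 0.800 | 73/365 = 0.200 |
| 0 (no supply) | 0.000 | 1.000 |

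The displayed value rises with supply and the worded value falls, so the order of patients is reversed.

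**Several drugs in one regimen.** Supply days are summed. Two drugs with 345 days each give 690/365 = 1.89 by the display. A share of days cannot exceed 1, and no cap is stated for RNP. Writing 1 minus the displayed ratio would not repair this: 1 − 1.89 = −0.89. Calendar days must be counted, each once.

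**The wording also needs a rule.** Take two drugs in one regimen, one covered for 365 days and the other for 265.

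- A day counts if any drug is missing: 100/365 = 0.27.
- A day counts only if no drug of the regimen is supplied: 0/365 = 0.

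The phrase in "calculated as the total number of days the patient did not receive one or more medications" points to the first reading. The interchangeability rule given for MPRs points to the second. The same sentence also speaks both of each regimen and of any of the patient's regimens, so it does not settle whether RNP is one value per regimen or one per patient.

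**The case against.** The strongest reply is that the reversal is conditional. The variable's name, its gloss and a full verbal definition stand directly above the formula and all point the right way, so a careful analyst would probably notice the slip. That stands: the protocol contradicts itself, and the reversal occurs only if the display is what gets programmed. A reader might infer that a benefit of the intervention will be published as more days without medication. The document does not support that as a prediction.

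A reader might also infer that a primary outcome is compromised. The first primary outcome in section 1.3 is medication adherence in general terms, and RNP is one of the three formulas listed for it. But RNP is not named in section 1.3. Section 1.4 expects the improvement in adherence to show in the MPR and the questionnaire. The sample size in section 2.10 uses the MPR, and section 2.8.1 introduces RNP as an addition to it. No named outcome depends on the faulty line.

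It is also tempting to quote a multiple. At the pilot mean MPR of 0.93 (section 2.10) the two versions give 0.93 and 0.07, a ratio of about 13. At the 0.80 threshold the ratio is 0.80/0.20 = 4. The multiple depends on the value chosen. It also treats the MPR as unique-day coverage, which holds only for a single drug without overlapping fills. The direction is the finding.

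An extraction fault is unlikely, because the equation is complete and the neighbouring MPRs formula was read intelligibly.

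**Conclusion.** The point holds as an internal contradiction in section 2.8.1. The displayed RNP formula is a possession ratio and runs opposite to the verbal definition. If it is used, full supply scores 1, no supply scores 0, and the protocol's 345-day example scores 0.945 instead of 0.055. These values assume one drug, non-overlapping fills and 365 days of follow-up. With several drugs the displayed ratio has no upper limit at 1.

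The reach is narrow. RNP is a supplementary adherence measure, and neither a named primary or secondary outcome nor the sample size is affected. The line should still be corrected before RNP is computed, because the protocol gives one variable two opposite definitions.

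**What to change.** Replace the displayed formula by

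RNP = (calendar days in follow-up without medication for that regimen, each day counted once) / (follow-up days),

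calculated separately for the antihyperglycaemic, antihypertensive and antihyperlipidaemic regimens.

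In the same edit:

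1. Make the sentence refer to one regimen at a time throughout.
2. State whether a day counts when any drug of the regimen is missing or only when no drug of the regimen is supplied, and reconcile that choice with the interchangeability rule used for MPRs. The authors should make this choice explicitly, because changing the numerator alone leaves it open.

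The cost is one formula, one sentence and the matching line of code. Counting unique days needs fill dates as well as days of supply. The protocol already plans to record refills for each medication class from the electronic record, so no new data source should be needed.
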